# Pilot Study of Home-Based Virtual Reality Fitness Training in Post-Discharge Rehabilitation for Patients with Spinal Cord Injury: A Randomized Double-Blind Multicenter Trial

**DOI:** 10.3390/life14070859

**Published:** 2024-07-09

**Keywords:** spinal cord injuries, clinical trial protocol, intervention, virtual reality, physical fitness

## Abstract

Spinal cord injury (SCI) patients require continuous rehabilitation post-discharge to ensure optimal recovery. This study investigates the effectiveness of home-based virtual reality fitness training (VRFT) as a convenient and accessible rehabilitation method for SCI patients. This randomized, double-blind, multicenter trial will enroll 120 participants, assigning them to either an 8-week VRFT program (exercise group) or a control group engaging in regular daily activities. The outcomes measured include muscle function, cardiopulmonary fitness, body composition, and physical performance. Our study will determine the safety and feasibility of VRFT in a home setting for SCI patients and evaluate whether these patients can effectively participate in such a program post-discharge. The results of this study are expected to inform future exercise protocols for SCI rehabilitation, offering valuable insights into the utility of VRFT as a therapeutic tool.

## 1. Introduction

Spinal cord injury (SCI) patients face various deficiencies due to the extent of their injuries and disabilities [1,2]. This population experiences severe physical impairments and substantial psychological and social consequences, affecting their quality of life [3,4]. The prevalence of SCI is significant, with approximately 2500 new cases reported annually in South Korea [5].

Many SCI patients endure prolonged hospital stays for initial treatment and rehabilitation. During this period, the central nervous system exhibits heightened neuroplasticity, facilitating potential functional improvements [6,7,8,9]. Early and intensive rehabilitation interventions have been instrumental in enhancing outcomes for SCI patients, reducing morbidity and improving overall quality of life. Nevertheless, managing SCI patients post-discharge remains a critical challenge to ensure continued recovery and successful reintegration into the community [3,4,8,9,10]. The efficacy of rehabilitation is heavily influenced by the intensity and specificity of the therapy, with repetitive, task-oriented, and intensive therapies being the most effective [11,12]. Therefore, continuous and intensive treatment is crucial for SCI patients to achieve optimal recovery [13].

Typically, SCI patients are offered outpatient therapy post-discharge. However, attending these sessions is often challenging due to long travel distances, inclement weather situations, and transportation problems [13]. Furthermore, due to high demand, patients often face long waiting periods and are given a restricted number of sessions.

SCI patients present a wide range of rehabilitation needs due to the extent of their injuries and the resulting disabilities. The diverse deficiencies include motor and sensory impairments, autonomic dysfunction, and secondary conditions such as pressure sores, spasticity, and chronic pain. Training conducted at home has the potential to significantly enhance access to rehabilitation for SCI patients, allowing them to extend their training period and potentially achieve better outcomes [13]. According to rehabilitation guidelines, individuals should take part in independent training, focusing on daily targets to guide their efforts [14,15].

Simulated training, such as virtual reality training, leverages computer systems to monitor user movements, facilitating interaction with on-screen games or activities. This technology ensures a reliable, user-friendly, and engaging recovery process for SCI patients, free from usage constraints [16,17,18]. In particular, virtual reality fitness training (VRFT) has the advantage of enabling participants to exercise through a game-based program that uses their physical abilities in real time [18]. Various research has demonstrated that VRFT positively impacts several physical health domains, including muscle function, cardiopulmonary fitness, body composition, and physical performance in SCI patients. Studies have shown that VRFT matches or surpasses the effectiveness of conventional therapy [16,17,19,20,21,22]. By providing interactive and integrated sensory game experiences that engage the entire body, VRFT serves as a substitute for conventional training [23]. This variation significantly alleviates the repetitiveness of conventional therapy, making workouts more fun. Implementing game-based techniques and immersive environments has shown promise in motivating individuals with SCI to participate in more rehabilitation training after being discharged from the hospital [23]. This optimistic outlook on the effectiveness of these methods is encouraging for the future of SCI rehabilitation.

This approach promotes participants’ engagement in vigorous physical activities by minimizing the dependency on assistant intervention. Thus, VRFT serves as a valuable addition or substitute to conventional therapy programs, potentially significantly enhancing patients’ quality of life after hospital discharge.

A variety of studies have examined the effectiveness of home-centered VRFT in enhancing fitness variables and rehabilitation post-SCI, indicating the feasibility of VRFT platforms for ongoing in-home recovery [18,24,25,26,27]. Nevertheless, patients with SCI involved in home-centered VRFT programs require well-defined methods to assess their functional capacity, identify physical limitations, and enhance their health condition and progress after hospital discharge. Various studies have indicated that individuals found home-centered VRFT satisfactory, although the specifics of program implementation can differ widely [18,23,24,27,28]. Barriers to using home-based VRFT include insufficient technological experience among users and technical issues [24].

Home-centered VRFT has the potential to serve as an addition or substitute to conventional rehabilitation programs for patients with SCI, with the possibility of significantly enhancing their quality of life [17,19,20,21,23]. Consequently, VRFT platforms appear promising for facilitating rehabilitation at home.

Game-centered VRFT helps to alleviate the boredom often associated with traditional exercise therapy by incorporating captivating and sensory elements. Virtual reality training provides an engaging and effective way to maintain physical activity by involving users in interactive settings and promoting exercises that engage the whole body [23,25]. Using gamified techniques and immersive environments, individuals with SCI show greater encouragement to participate in a workout [23,26]. Consequently, home-based VRFT minimizes the need for direct intervention, fosters vigorous physical activity, and increases engagement more effectively than in hospital environments [27,28].

The American Spinal Injury Association encourages patients with SCI to improve their physical health, emphasizing muscle function, physical performance, cardiopulmonary fitness, and body composition [28]. Nevertheless, numerous individuals with SCI residing in the community after hospital discharge are involved in activities that lack sufficient physical activity or do not effectively support functional recovery [11]. Moreover, the engagement of individuals with SCI in house-centered exercises is restricted, highlighting the need for more secure exercise options [14]. One novel approach involves home-centered VRFT, supported by a physician’s prescription, to guarantee patient safety during exercise sessions.

SCI patients who have transitioned from hospital-based rehabilitation to the community should be evaluated on the effectiveness of a VRFT customized to their health condition based on their condition and medical prescription. Nevertheless, to date, the Republic of Korea lacks research examining the safety of house-centered VRFT participation for individuals with SCI discharged from hospital when guided by a physician’s prescription. Therefore, our research group, comprising experts in exercise and rehabilitation medicine, intends to examine the impact of house-centered VRFT on individuals with SCI following discharge from hospital, under the guidance of a physician’s prescription.

## 2. Methods

### 2.1. Experimental Design

This trial is structured as a multicenter, randomized, double-blind, parallel group that focuses on individuals with their first spinal cord injury. Random assignment of individuals to the exercise or control group will be allocated with evaluators unaware of group placements during subsequent assessments.

The study design ensures that all participants receive the standard care appropriate for their condition. The control group will continue their usual daily routines without additional exercise interventions, reflecting a real-world scenario where not all patients may have access to or engage in structured rehabilitation programs. This design allows us to evaluate the additional benefits of the VRFT program. Any participant identified as needing further rehabilitation will be referred for appropriate care, ensuring no one is deprived of necessary medical support.

The trial will be conducted at four distinct hospitals across South Korea: (1) National Rehabilitation Center and Hospital, (2) Bucheon SM Hospital and Sports Center, (3) Goyang Rehabilitation Sports Center and Korea National Health Insurance Service Hospital in Ilsan, and (4) Goodplayground Center and Korea University Anam Hospital.

Eligible participants will be enrolled in the spinal cord injury rehabilitation programs at the involved hospitals, which cater to both inpatients and outpatients. During the study, an investigator will evaluate with the participants’ consent and remain unaware of their group assignments.

The research protocol will commence under the direction of the National Rehabilitation Hospital. This study received approval from the Institutional Review Board at the National Rehabilitation Hospital (National Rehabilitation Ceter-43-5-2021). Registration of the study protocol was completed with the identifier KCT0007521. This protocol adheres to the SPIRIT guidelines [29]. A flowchart outlining the study design is illustrated in Figure 1.

### 2.2. Participants

Participants may be eligible for the study if they (1) have been diagnosed with SCI, (2) have completed their initial hospitalization and rehabilitation, and are now living in the community, and (3) have provided informed consent and are willing to participate in this research. To address ethical concerns, all participants, including those in the control group, will continue to receive standard care and support as per clinical guidelines. Those requiring immediate or additional rehabilitation will not be excluded from receiving necessary interventions outside the scope of the study. Participants will not be eligible for the study if they (1) are presently receiving inpatient care, (2) cannot participate in exercise activities because of other nervous system disorders (apart from SCI), lower limb orthopedic issues, or severe cardiovascular or respiratory conditions, and (3) are assessed by the evaluator as unable to perform the required tasks.

### 2.3. Randomization

Following the acquisition of informed consent from the participants, each team supervisor will identify and refer suitable candidates for the study. Subsequently, an independent statistician, not affiliated with the study team, will conduct the randomization process. Within each institution, participants will be categorized into two distinct subgroups through a block randomization approach. By employing blocks of size two in each stratum, an equal distribution ratio of 1:1 between the experimental and control groups will be achieved.

The randomization schedule will be generated utilizing SPSS software version 23.0 (IBM Corp., Armonk, NY, USA). The statistician responsible for the randomization will determine the block size and seed number through a random selection process. Thereafter, the randomized allocations will be sealed in packets, each designated for a participant, and delivered to the manager when the trial begins.

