### 2.4. Random Assignment

The research implements a double-blind methodology ensuring that neither the individuals involved nor the assessors know the allocation of the groups. To maintain blinding, independent assessors who are unaware of the group assignments will conduct all evaluations. Additionally, participants will be instructed not to discuss their specific activities with the assessors or other participants. Trainers administering the interventions will be kept unaware of the study details to minimize possible prejudice to the integrity of outcomes, thus strengthening the research results’ validity. Nonetheless, it should be noted that the principal investigator conducting the study will be aware of the group assignments due to the nature of the trial. Participants in the control group will adhere to their usual daily routines without any additional exercise intervention. They will continue with their regular activities of daily living (ADLs) as they did before the study, without any structured or guided exercise program.

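### Section 2.3 contradicts itself on block size; if blocks of two are used with one-by-one enrolment, up to half of the assignments could be known in advance

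*Protocol article*

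**What the plan says.** Section 2.3 stratifies by site: "Within each institution, participants will be categorized into two distinct subgroups through a block randomization approach". It names one block size, "By employing blocks of size two in each stratum", and draws the consequence that "an equal distribution ratio of 1:1 between the experimental and control groups will be achieved".

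The next paragraph of the same section says: "The statistician responsible for the randomization will determine the block size and seed number through a random selection process". It lists no set of sizes and does not say whether the size varies from block to block.

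Concealment rests on an independent statistician and on packets: "the randomized allocations will be sealed in packets, each designated for a participant, and delivered to the manager when the trial begins". Candidates come from the sites: "each team supervisor will identify and refer suitable candidates for the study".

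On who can see the arms, Section 2.4 states that "the principal investigator conducting the study will be aware of the group assignments". Section 2.6 has research staff supervising the exercise group, who use a game console and a ring controller, while the comparison group receives no intervention and no sham. Section 2.4 also says that outcome assessors are independent and unaware of allocation.

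**The concern.** There are two problems.

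The first is the contradiction. A size already given as two and a size still to be drawn at random cannot both describe the list. A statistician working from this text could build either.

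The second is what follows if two is the size used. A block of two at 1:1 has only two forms, exercise then control or control then exercise. Once the first assignment of a pair is seen, the next is known. Sealed packets stop someone from reading the next allocation early; they do not stop someone from inferring it.

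Foreknowledge has a route to act. Referral is at the discretion of site supervisors, and Section 2.2 contains a judgement-based exclusion for people who "are assessed by the evaluator as unable to perform the required tasks". Who is put forward, and when, could therefore depend on the assignment that is coming. Such selection happens before randomization, so intention-to-treat analysis does not remove it. The t-test and Mann–Whitney comparisons named in Section 2.9 would carry it into the estimated effect. Blinded assessors protect measurement, which is a separate matter from concealment.

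**Working it through.** **Inputs**

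- Block size 2, ratio 1:1, stratum = institution (Section 2.3).
- Four sites (Section 2.1) and 120 participants (Abstract, Section 2.9). Equal site sizes are assumed, which gives 120 / 4 = 30 per site. This agrees with the 15 per exercise group in the Discussion: 4 × 15 = 60.

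**The plan's own figure.** Blocks of two give 30 / 2 = 15 blocks per site, hence 15:15 per site and 60:60 overall. The stated 1:1 ratio is reproduced.

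**Predictability of fixed blocks.** The observer is assumed to know the block size, where blocks begin, and all earlier allocations at the site. For a block of 2b participants at 1:1:

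- share of assignments known with certainty = 1 / (b + 1)
- share guessed correctly by always naming the arm with more places left = [b + 2^(2b−1) / C(2b, b) − 1/2] / (2b)

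For blocks of two (b = 1): the certain share is 1/2, and the guessed share is [1 + 2/2 − 1/2] / 2 = 0.75.

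For blocks of four (b = 2): 1/3, and [2 + 8/6 − 1/2] / 4 = 0.708.

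For blocks of six (b = 3): 1/4, and [3 + 32/20 − 1/2] / 6 = 0.683.

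Listing every possible sequence for each block size gives the same values.

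**Randomly varied sizes.** These were simulated with 30 participants per site and 4,000 replicates. The observer knows which sizes are possible and all earlier allocations, but not where blocks begin and end, and updates the probabilities after each allocation.

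| Scheme | Certain | Of 120 | Guessed correctly |
|---|---|---|---|
| Blocks of 2 | 50.0% | 60 | 75.0% |
| Blocks of 4 | 33.3% | 40 | 70.8% |
| Blocks of 6 | 25.0% | 30 | 68.3% |
| Mixed 4 and 6 | about 5.6% | about 7 | about 69% |
| Mixed 4, 6 and 8 | about 2.4% | about 3 | about 67% |
| Unrestricted | 0% | 0 | 50% |

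The rows for fixed sizes are for complete blocks.

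Mixing sizes mainly removes certainty. Guessing improves little, because any scheme that forces balance within short runs makes the under-filled arm the better bet.

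**Imbalance under the mixed scheme.** The worst case at one site is to stop after three same-arm assignments in a block of six, a difference of 3. Over four sites the most is 4 × 3 = 12.

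**The case against.** Four points on the other side have force.

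1. *The rule is not settled.* A reader might infer that blocks are fixed at two. Section 2.3 names that size but also describes a random choice of block size, so fixed blocks of two are one reading of a contradiction. This stands. It does not clear the text, though: a single size drawn at random that came out as two would be just as predictable.

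2. *Allocation may not be sequential.* The packets are each designated for a participant and handed over at the start of the trial. This can be read as candidates being identified first and then allocated together, in which case no referrer faces a next assignment to exploit. This reading is possible. The article states neither it nor rolling enrolment, so the size of the problem has to be given conditionally.

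3. *The chain of knowledge is inferred.* Supervisors refer, whereas the principal investigator is the one named as knowing assignments. Nothing says that the principal investigator refers, or that the supervisors are the research staff who oversee the exercise group. Consent, referral and baseline assessment also come before randomization, which narrows the room to act. All this stands as a limit. Against it, one arm has equipment and supervised classes and the other has nothing, so earlier allocations at a site would be hard to hide from its staff.

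4. *Safeguards exist and the trial is a pilot.* The independent statistician protects the making of the list and the blinded assessors protect measurement. Neither makes the next assignment harder to infer.

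A reader might also infer that an assessor who learns one participant's arm can work out the partner's. That would require knowing which two people form a block, and nothing in the article suggests that assessors see the randomization order.

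**Conclusion.** The contradiction on block size holds on any reading and must be reconciled.

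The predictability point holds conditionally. With blocks of two, up to 60 of 120 assignments could be known in advance and 75% guessed correctly, against 50% with no foreknowledge. This assumes that participants are allocated one by one within a site, and that whoever refers them knows the block size, which the article publishes, and the previous allocation at that site. The count of 60 also assumes that every site completes its blocks.

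These figures are a ceiling. It would be tempting to conclude that concealment fails for half of the participants. The article makes the needed knowledge plausible because the arms are visible, but it does not show that referrers have it, or that any selection has occurred.

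**What to change.** In Section 2.3:

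- Remove the stated block size of two. Say instead that permuted blocks of randomly varied sizes (for example 4 and 6) will be used within each site, with sizes generated and held by the independent statistician and not disclosed to sites.
- Keep the sentence on random selection, but reword it to say that sizes vary at random between blocks. As it stands, it could mean one draw of a single size for the whole trial.
- Reissue packets not yet used from the new list.

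With sizes 4 and 6, certain assignments fall from 50% to about 6%. Correct guesses fall only from 75% to about 69%, so the gain should be described as removing certainty, not as ending guesswork.

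The cost is a new list, the reissued packets, and an imbalance of up to 3 participants at any site that stops mid-block, at most 12 over the four sites.

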### 2.4. Random Assignment

The research implements a double-blind methodology ensuring that neither the individuals involved nor the assessors know the allocation of the groups. To maintain blinding, independent assessors who are unaware of the group assignments will conduct all evaluations. Additionally, participants will be instructed not to discuss their specific activities with the assessors or other participants. Trainers administering the interventions will be kept unaware of the study details to minimize possible prejudice to the integrity of outcomes, thus strengthening the research results’ validity. Nonetheless, it should be noted that the principal investigator conducting the study will be aware of the group assignments due to the nature of the trial. Participants in the control group will adhere to their usual daily routines without any additional exercise intervention. They will continue with their regular activities of daily living (ADLs) as they did before the study, without any structured or guided exercise program.

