### 2.6. Program

The training program consists of 1 h classes conducted biweekly over a period of 2 months, as detailed in Table 1. Participants in the exercise group will have access to the VRFT devices not only during the biweekly classes but also at home throughout the trial period. This will allow the participants to engage in additional sessions as desired.

The rehabilitation protocol for spinal cord injury comprised cardiovascular and strength training exercises, as well as practical exercises focusing on the extremities and core. Furthermore, specialized programs were designed considering the goals and the type of exercise, time, frequency, duration, and intensity, adhering to the guidelines of the American College of Sports Medicine. The intervention program will incorporate the use of the Ringfit Adventure (RA) game for the Nintendo Switch (NS). (Figure 2). RA, a fitness program for the Nintendo, utilizes semi-immersive technology.

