Individuals with SCI will require an NS system, a Ring-Con (RC) (a flexible exercise ring held by the participant), a Bluetooth operator (attached to the RC and the other fastened to a leg strap on the participant’s quadriceps), and a monitor for this training class. The class is scheduled twice a week over eight weeks. Each class will be 1 h long, consisting of 10 min for warming up, 10 min for cooling down, and 40 min dedicated to the primary exercise session. RA is an action role-playing fitness game that advances the storyline through the player’s physical activities, which directly influence the character’s on-screen movements. These exercises are performed with the aid of the RC and thigh band [30]. The RC contains highly accurate pressure and tension detectors that capture and translate the individual’s movements [31]. Additionally, the Bluetooth operator features an infrared motion sensor capable of tracking the participant’s pulse rate [32]. RA has the capability to assess the ideal intensity of physical activities tailored to each individual and modify it according to biological signals either lowering or raising the activity level. In the first class, the virtual coach determines the intensity of physical activities and then progressively modifies them according to feedback from later sessions. The research staff will consistently supervise individuals in the exercise group, who will encourage participants to sustain the 16-session class at 60% to 80% of the individual’s baseline and the highest heart rate. Participants will be guided to keep their exertion within the range of 4 to 8 on the modified Borg CR10 rating of perceived exertion scale, which translates to a perception of effort from ‘moderate’ to ‘vigorous’ [33]. Participants in the comparison group will adhere to their normal routines and will not receive any specific intervention throughout the study.

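### The plan says participants do not know their allocation, but a console exercise programme against usual routines without a sham can be assessor-blinded at most

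*Protocol article*

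**What the plan says.** Section 2.1 of the protocol article gives the label: "This trial is structured as a multicenter, randomized, double-blind, parallel group". Section 2.4 spells out what the label means: "The research implements a double-blind methodology ensuring that neither the individuals involved nor the assessors know the allocation of the groups". The title, the Abstract and the opening of the Discussion repeat the double-blind description.

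On the comparison itself, section 2.4 says: "Participants in the control group will adhere to their usual daily routines without any additional exercise intervention". Section 2.6 repeats it: "Participants in the comparison group will adhere to their normal routines and will not receive any specific intervention throughout the study". For the other arm, section 2.6 says: "Participants in the exercise group will have access to the VRFT devices not only during the biweekly classes but also at home throughout the trial". It also says: "The research staff will consistently supervise individuals in the exercise group". Sections 2.1 and 2.2 add that everyone, controls included, goes on receiving standard care and is referred if further rehabilitation is needed.

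**The concern.** Section 2.4 claims more than a loose label does: it asserts that the participants themselves are unaware of their group. Someone who has, or has not, been given a games console, a ring controller, a leg strap and two classes a week knows which group they are in.

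What is at stake is how the results may be read. A double-blind label tells readers that neither participants' expectations nor the assessors' knowledge could have moved the outcomes. If only the assessors are blinded, the first of these protections is missing. Many of the outcomes are of the kind that expectation and motivation can move. The limitations paragraph in the Discussion speaks of small numbers and does not mention this.

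**Working it through.** No arithmetic applies, and the plan gives no figure for this point. The check sets the statements side by side.

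1. **What is claimed.** Section 2.4 says that participants and assessors are both unaware of allocation.

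2. **What each arm receives.**
   - Exercise arm (2.6): the console game with ring controller and leg strap, two one-hour classes a week for eight weeks (2 × 8 = 16 sessions), supervision and encouragement by research staff, home use of the device, and standard care (2.1, 2.2).
   - Control arm (2.1, 2.2, 2.4, 2.6): usual routines and standard care.
   - The statements in 2.4 and 2.6 that controls get no additional or specific intervention rule out a sham or attention control. This is therefore not a detail that the article may simply have left to a fuller document.

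3. **What participants are told.** Under 2.5 the investigators explain the study in detail before consent. Participants will then see which of the two conditions they have been given.

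4. **What the blinding measures do.** Section 2.4 lists three.
   - Independent assessors unaware of group: this blinds assessors.
   - An instruction to participants not to talk about their activities with assessors or each other: this protects assessor blinding, and it presupposes that participants know what they are doing.
   - Trainers kept unaware of study details: this does not conceal a participant's own group from that participant.

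   None of the three blinds participants.

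5. **What section 2.1 says about the mechanism.** "Random assignment of individuals to the exercise or control group will be allocated with evaluators unaware of group placements during subsequent assessments". Only evaluators are named. This fits assessor blinding and does not support the claim in 2.4 about participants.

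6. **Which outcomes are exposed.**

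| Measure (section) | Depends on participant effort or self-report at testing |
|---|---|
| Grip strength (2.7.1) | Effort |
| VO2peak, ended by voluntary exhaustion (2.7.2) | Effort |
| Spirometry, MIP and MEP (2.7.2) | Effort |
| Functional reach (2.7.3) | Effort |
| DXA and bioimpedance (2.7.4) | Little |
| WHOQOL-BREF (2.7.5) | Self-report |

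Section 2.7 makes muscle strength, cardiopulmonary fitness, body composition and physical performance the primary outcome. Three of these four primary domains therefore rest on effort-dependent tests.

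**The case against.** The best defence is that the trial's conduct is already described honestly. The control condition is stated openly in several sections, section 2.1 describes assessor blinding in operational terms, and any experienced reader can see that participants cannot be masked. Correcting the label changes nothing in the randomisation, sample size, outcomes or tests, and the bias remains afterwards. All of this is true, and it limits the point to a correction of wording. It does not rescue the sentence in 2.4, which is a positive statement and is wrong as written. Nor does it help to suppose that participants are unaware of the hypothesis, because the text speaks of allocation.

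Several stronger readings are tempting but are not supported:

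- **That controls get nothing.** Sections 2.1 and 2.2 give them standard care. The contrast is the programme plus standard care against usual routines and standard care.
- **That the assessors are unblinded too.** Independent assessors and the non-disclosure instruction make assessor blinding plausible. The principal investigator's knowledge of allocation is disclosed in 2.4, where all evaluations are assigned to independent assessors.
- **That the bias has a known size.** The documents give no estimate. Any fraction of the planned effect size of 0.5, or any inflated false-positive rate, would only return the value assumed.
- **That body composition is immune.** DXA and bioimpedance are less open to effort and reporting bias at the test. Unblinded participants may still change their behaviour outside the programme, and that could alter body composition.
- **That the registry entry is wrong.** Only its identifier is given, so its masking field cannot be judged here.

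**Conclusion.** The concern holds in this form. The statement that participants do not know their allocation, and the double-blind label in the title, Abstract, 2.1, 2.4 and Discussion, contradict the design described in 2.4 and 2.6. The supportable description is assessor-blinded with participants unblinded.

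The contradiction concerns every participant, 120 as planned. It bears on the interpretation of grip strength, VO2peak, spirometry, MIP and MEP, functional reach and WHOQOL-BREF. Bias in these is possible, not demonstrated, and its size cannot be derived from the documents. The conclusion rests on no numerical assumption. It needs only that participants can tell whether they have been given the device and classes.

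**What to change.** - Replace double-blind with assessor-blinded (participants unblinded) in the title, Abstract, 2.1, 2.4 and Discussion.
- In 2.4, delete the claim that participants are unaware of their allocation. Keep the instruction not to disclose activities to assessors.
- Add to the limitations that grip strength, VO2peak, spirometry, MIP and MEP, functional reach and the self-reported WHOQOL-BREF are open to participant-expectation bias, which assessor blinding does not remove. Add that DXA and bioimpedance are less open to effort and reporting bias at testing but are not protected from performance bias.
- Optional: have assessors record their guess of allocation at the post-test, as a check on the blinding that the trial does have.
- Amend the registry only if it carries the same wording.

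The cost is a wording amendment, plus one item on the assessment form if the optional check is adopted. Randomisation, sample size, outcomes and planned tests stay as they are. The description becomes less favourable but accurate.
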